#### Secondary Trial Outcomes

The secondary outcome of the trial will be changes in the dietary intakes and nutritional status of adolescents at school.

### Process Evaluation of the Intervention

Two methods will be used for process evaluation of the intervention, namely external and internal audit using a checklist and qualitative assessment.

#### External and Internal Audit

The process of evaluation will include a checklist for Healthy School Canteens by dietitians to check the availability of healthy food and drink options, cooking with less oil or less salt, preparing more low energy-dense *kuih*, putting extra vegetables in some dishes and ensuring they provide fewer foods from the amber group and more foods from the green group. Furthermore, there will be an observation (log) of the training for the canteen and school convenience shop operators. The Healthy School Canteen Checklist will comprise five sections; two sections on the vendor and school information (section A and B), three evaluation sections where the basic criteria will be evaluated for healthy dishes (section C), healthy food serving method (section D), and traffic light method (section D). Each of the three evaluation sections will carry a percentage for a total score of 100%. Section C will account for 45%, while sections D and E will account for 20 and 35% of the assessment scores (see Supplementary Material 2). The assessment scores must be ≥80% to be recognised as a healthy cafeteria based on MOE Healthy Canteen Guidelines.

The dietitians will have access to the canteen, observe, and check, and they will ask questions about cooking methods. Before the evaluation period using the Healthy School Canteen Checklist, two external dietitians will be trained to ensure consistency in data evaluation. Each external dietitian will be independently assigned to evaluate the same intervention schools (canteen and school convenience shop vendors) over the 4-week period. Any discrepancies arising between two qualified and trained dietitians will be resolved via discussion between the two dietitians, when an agreement could not be reached, a discussion will be held with the principal investigator.

#### Qualitative Assessment

The use of qualitative research methods is essential to gain insights into the implementation process and context and participants' perspectives on the intervention. Qualitative methods will be used to assess the acceptability and feasibility of the interventions, as well as the study procedures. Interviews with canteens and school convenience shop operators will be conducted to explore the acceptability and barriers in the implementation of the proposed intervention, and their understanding of healthy and unhealthy foods based on the traffic light concept. A total of 12 participants, one canteen operator and one school convenience shop operator per intervention school will be asked about any changes in cooking methods after the training sessions and any changes in their knowledge and attitudes toward preparing healthy foods, which should be reflected in their cooking practices. In addition, focus groups will be conducted with adolescents to explore their opinions on the availability of healthy food and acceptability of the food environment. A total of 80 students will participate in focus groups, 20 per intervention school (10 boys and 10 girls), and they represent the major ethnic groups in Malaysia (Malay, Chinese, Indian). Interviews with school teachers (*n* = 12) will also be conducted to obtain their feedback for the changes at canteens and school convenience shops. The interview guide is as attached in the Supplementary Materials.

### Planned Analysis

Feasibility studies are not designed to evaluate the effectiveness of interventions (54). As this is a feasibility study, no formal comparison between the study arms will be undertaken and no significance testing will be conducted. Descriptive statistics such as the mean (standard deviation) for continuous variables and frequency and proportions (*n*, %) for categorical variables will be used to evaluate the research hypotheses. In light of the feasibility study and the associated lack of statistical power, all effects will be evaluated based on effect size and *p*-values will not be reported. The analysis will be reported using the relevant CONSORT checklists (55). For quantitative data analysis, the SPSS software (Version 25.0, Chicago, IL, US) will be used. All focus group discussions and interviews will be audio-recorded, transcribed verbatim and entered into NVivo software to analyse quantitative data and facilitate data coding. Field notes and memos will be also analysed and the framework approach for qualitative data analysis will be used (56).

### Participant Confidentiality

All study personnel will be trained in the requirements to ensure the participants' confidentiality. The principal investigator will protect the confidentiality of participants' information. Participant identification code will be assigned upon study enrolment. The data will be kept centrally by the principal investigator and will be anonymised and identified by a unique code. Moreover, access to personally identifiable information will be limited to members of the research team. Documents that will not be anonymised, such as signed informed consent forms will be held by the principal investigator in a locked cabinet in the department at the university.

## Discussion and Conclusion

The MyHeARTBEaT study proposes the design and rationale for a school-based intervention to facilitate the adoption of a healthy canteen policy in Malaysian schools. The study will try to determine if the audit and subsidisation for healthy foods can improve/increase the availability of the healthy food and drinks option at the school canteen and convenience shop, improve the number of school canteens, which offer healthy food options, increase the number of students who consume greater amounts of fruits and vegetables, and decrease the intake of SSBs by students. This strategy may have the potential to offer cost-effective and sustainable support to improve the school canteen food environment. The insights into the effects of price-related approaches to improve food consumption and purchasing behaviours may provide evidence to build appropriate policy and programme responses to the epidemic of obesity and poor diet quality currently facing Malaysian adolescents (49).

Limited healthy lifestyle school-based interventions were conducted in Malaysia. As such, this study addresses a significant research gap and a potentially valuable missed opportunity in efforts to promote healthy eating behaviours among Malaysian adolescents. The research may contribute to the literature on the adverse effects of poor nutrition and associated adverse health outcomes, including obesity, in the Malaysian population and worldwide. While the impacts of school-based canteen interventions have been examined in other studies in Malaysia, the upcoming trial will be the first to analyse the impact of healthy food subsidisation in Malaysian school canteens and targeting both school convenience shops and canteens for intervention. The intervention will be considered to warrant evaluation via a full trial if the study achieves more than 50% of all healthy canteen menu items in the “GREEN” category and recruits 80% of eligible participants. Based on this feasibility, we shall plan either to use interventions such as training of canteen and school convenience shop operators only (intervention 1) or training with some financial subsidy (intervention 2) for the full trial.

This school-based study is intended to provide new insights regarding the implementation of healthy foods and drinks environment in Malaysian schools, including distribution of subsidised fruits and vegetables and low ED *kuih* that may improve healthy food intake among Malaysian adolescents. The possible implication of this study includes minimizing the availability of SSBs sold in school canteen in the future. We also want to see the availability of fruits and vegetables at the school canteen and the acceptance of healthier food options among the school adolescents. By offering more of healthier option of foods and beverages in school, it will be good to evaluate if changes toward environment may enable the students for better healthy options. From this healthy canteen and convenience shop interventions, we would like to see any changes on anthropometric measurements within a month of intervention. This will enable us to plan for larger scale study in the future. With all the intervention planned, it is anticipate it should be acceptable as we do take into account the diversity of Malaysian ethnic background.

This study is anticipated to be useful in intervention development process and identifying ways to improve the availability of healthy foods within the school environment and modifying healthy canteen guidelines and policy development. It is expected that the findings from this study can provide a framework for the conception and implementation of nutritional interventions at the school canteens in Malaysia that will be tested for efficacy in a future definitive trial.

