Several initiatives have been implemented in Malaysia and across the world to ensure adherence to established nutritional guidelines and standards, healthy canteen policies, and strategies for all foods served in school canteens (34–36). However, the impact of these programmes and their long-term sustainability are unclear. Addressing this gap is particularly important in Malaysia, where the school is an important provider of two main meals (breakfast and lunch) (37). In a recent systematic review about Malaysian adolescents' dietary intake, there was a small difference in dietary patterns according to ethnic diversity, which indicated that Malays had higher SSBs intake and lower diet quality than Chinese and Indian adolescents (21). Furthermore, Malay adolescents preferred Western-based and local-based dietary patterns while Chinese adolescents intended to follow a healthy-based food pattern, which may reflect the effect of socio-cultural diversity on food preferences (21).

In Malaysia, the schoolchildren purchased food from the canteen and *koperasi* (school convenience shop) which are run by the canteen operators and school administration, respectively. The *koperasi* sells mostly energy-dense snacks and beverages. The staple foods usually was sold at the canteen such as noodles, fried rice, nuggets, and fried chicken, energy-dense traditional cakes (e.g., *Rempeyek, Kuih Peneram, Kerepek Ubi Kayu, Kuih Baulu*, etc.), and SSBs.

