Trained dietitians will audit the canteen menu and food items sold by the school canteen and convenience shops in all schools (during the 4-week intervention phase, once a week). The menu audit process has been implemented in other studies (45). The study outcome measures will be assessed at the individual level and will consist of a 3-day diet history assessment and anthropometric measurements that will be conducted at baseline and post-intervention (4 weeks after intervention). Focus group discussions with students who will be involved in the intervention and interviews with teachers, school headmasters, and canteen operators will be conducted post-intervention to explore the acceptability and barriers in implementing the proposed intervention (see Supplementary Material 1). Estimation of sales will be done based on weekly receipts from the canteen and school convenience shop operators of healthy food items, such as vegetables, fruits, and low-calorie *kuih*. The data will be collected at baseline (August to September 2018) and the following intervention will be carried out after 3 months the year after (January to April). The summary of intervention assessment and logic model are shown in Figures 1, 2, respectively.

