### Intervention Overview

This study will explore the feasibility of conducting a dietary intervention in different types of schools (urban or rural) and its potential (evidence of promise) for improving healthy eating practices in adolescents from different socioeconomic backgrounds. It will focus on offering healthy food and beverage options in the school canteen and convenience shop. School canteens will be supposed to support healthy eating based on the healthy canteen guidelines designed by the Ministry of Education (MOE) (52). This will be achieved by increasing the availability and promotion of an extensive range of foods that should make up the majority of a healthy diet (GREEN). AMBER foods can be consumed only sometimes, choosing healthier alternative foods and avoiding large serving sizes that should be eaten in moderation. RED foods are “stop and think foods” that do not meet specified minimum nutrient criteria (RED). The intervention will try to overcome barriers to healthy canteen guidelines implementation and adherence. Specifically, the intervention will assist schools to remove “red-flagged” and “ban” food items from the canteen menu while increasing the availability of “GREEN” menu items. The objective will be to ensure more than 50% of all canteen menu items are in the “GREEN” category. Examples of “GREEN”, “AMBER,” and “RED” food items are indicated in Table 1.

**Table 1 T1:** Food classification description.

	**Everyday foods– “GREEN”**	**Select carefully– “AMBER”**	**Occasional foods– “RED”**
Nutritional quality	• High in nutrients and fibre. • Low in saturated fat and/or added sugar and/or salt.	• Moderate in added fat and/or sugar. • Contribute to excessive kilojoules if consumed in large serving size.	• Very low in nutritional value. • High in saturated fat and/or added sugar and/or added salt.

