### Outcomes

#### Potential Trial Outcomes

As this is a feasibility study, the focus of the current study will be whether the intervention can be delivered as intended and desired outcomes can be attributed. It is envisaged that if we have to move to a larger trial that the primary outcome will be the participants' consumption of healthy canteen items. The participants will be deemed as consuming healthy canteen items or green foods based on their dietary intake of more than 50% of listed menu items. The canteen operators will be tasked with auditing the green items available for sale at the school canteen. During follow-up, two dietitians will audit the results based on the canteen audit and discussion with canteen staff. Food classification tools and guidelines published by the Ministry of Education in Malaysia will be used to categorise the food (see Table 1).

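### The progression rule counts GREEN items against 'healthy' canteen items, the delivery target against all canteen items; read literally, the rule ignores RED items

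*Protocol article*

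**What the plan says.** All places are in the protocol article.

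- **Progression rule (Discussion and Conclusion).** A full trial is considered warranted "if the study achieves more than 50% of all healthy canteen menu items in the" GREEN category and the study "recruits 80% of eligible participants". These are the only two conditions. The next sentence says that the feasibility results will decide whether intervention 1 (training only) or intervention 2 (training plus subsidy) goes into the full trial.
- **Delivery target (Intervention Overview).** "The objective will be to ensure more than 50% of all canteen menu items are in the" GREEN category. The same section says that "the intervention will assist schools to remove “red-flagged” and “ban” food items from the canteen menu while increasing the availability of “GREEN” menu items".
- **Use of the word healthy (Potential Trial Outcomes).** "The participants will be deemed as consuming healthy canteen items or green foods based on their dietary intake of more than 50% of listed menu" [...]. Here healthy canteen items and green foods are alternative names for one thing.
- **Status of AMBER (External and Internal Audit).** The checklist looks at "ensuring they provide fewer foods from the amber group and more foods from the green group".

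**The concern.** The target and the progression rule share a numerator (GREEN items) and a threshold (more than 50%), but not a denominator. The target divides by everything on the canteen menu. The rule divides by the healthy part of it. A denominator limited to healthy items leaves out the RED items that the intervention is meant to take off the menu, so the ratio need not respond to the change it is supposed to certify.

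The rule decides whether a full trial goes ahead, and its other half, recruitment, says nothing about the menu. With two versions of the menu criterion in print, the choice between them could be made after the audit results are known.

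**Working it through.** The 50% threshold is a chosen cut-off, so there is no calculation in the article to reproduce. The check is what each denominator does to the same menu.

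**Notation.** G, A and R are the numbers of GREEN, AMBER and RED items on a canteen menu.

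**Three denominators**

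1. All canteen menu items (Intervention Overview): G / (G + A + R).
2. Healthy = GREEN (the progression rule read with Potential Trial Outcomes): G / G = 100% whenever G is at least 1.
3. Healthy = GREEN + AMBER (an assumption; the article never says this, and its wish for fewer AMBER foods sits badly with it): G / (G + A).

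R appears only in the first.

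**Illustrative menus.** The article gives no baseline menu counts, so these 40-item menus are assumptions. The fifth row is the fourth with all RED items taken off.

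| G / A / R | G / (G+A+R) | G / (G+A) | G / G |
|---|---|---|---|
| 2 / 3 / 35 | 2/40 = 5.0%, fail | 2/5 = 40.0%, fail | 100%, pass |
| 6 / 4 / 30 | 6/40 = 15.0%, fail | 6/10 = 60.0%, pass | 100%, pass |
| 8 / 16 / 16 | 8/40 = 20.0%, fail | 8/24 = 33.3%, fail | 100%, pass |
| 10 / 8 / 22 | 10/40 = 25.0%, fail | 10/18 = 55.6%, pass | 100%, pass |
| 10 / 8 / 0 | 10/18 = 55.6%, pass | 10/18 = 55.6%, pass | 100%, pass |
| 22 / 10 / 8 | 22/40 = 55.0%, pass | 22/32 = 68.8%, pass | 100%, pass |

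**Reading the table**

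- With healthy = GREEN, every menu passes, even one where GREEN is 5% of what is on sale.
- With healthy = GREEN + AMBER, some menus fail, so the rule is not automatic. But removing all 22 RED items (fourth row to fifth) leaves the ratio at 55.6%. The all-items share moves from 25.0% to 55.6% and crosses the threshold.
- With all items as denominator, the menus that are mostly RED or AMBER fail, and the two that meet the stated target pass.

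That R drops out of the second and third ratios is algebra and does not depend on the assumed menus.

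**The case against.** The best defence is that the extra word is a loose restatement. Healthy canteen is a fixed compound in this article (guidelines, booklet, policy), so the phrase can be read as all menu items of the healthy canteen, which is the denominator of the delivery target. The threshold, the word 'all' and the GREEN numerator match, and nobody would knowingly adopt a rule that GREEN items be mostly GREEN. This is a fair account of what was probably meant. It does not settle what is written, because Potential Trial Outcomes uses almost the same phrase to mean green foods.

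Four stronger readings are tempting, and the document does not support them:

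- **That the rule is met by definition.** This holds only if healthy means GREEN. It never holds for the whole rule, because the 80% recruitment condition is unaffected.
- **That the study cannot show whether the intervention was delivered.** The article also plans a canteen checklist with an 80% pass mark, a log of operator training, weekly audits, sales receipts and, in intervention 2, coupon counts and vegetable receipts. These exist; they are just not part of the progression rule.
- **That leaving out the convenience shop is a contradiction.** The shop "sells mostly energy-dense snacks and beverages", and it is an intervention target. But the delivery target is also canteen-only, so the two statements agree here. Nor would a shift of RED items to the shop go unseen: dietitians will "audit the canteen menu and food items sold by the school canteen and convenience shops in all schools" each week of the intervention.
- **That one arm can carry the other.** Arms at 40% and 65% would average 52.5%, but the article does not say that arms are averaged. It says only that the study must achieve the threshold.

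**Conclusion.** The inconsistency is real and lies in a decision threshold. The progression rule and the delivery target name different denominators for one 50% criterion. On the article's own equation of healthy canteen items with green foods, the menu half of the rule is 100% for any menu with a GREEN item. On the more generous GREEN-plus-AMBER reading, which is an assumption, it can fail but still cannot register the removal of RED items. On the assumed 10/8/22 menu the three denominators give 25.0%, 55.6% and 100%; the real gap depends on menus that the article does not describe.

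A drafting slip is the likeliest cause. That makes the correction easy, but it is still needed before the audit data are seen. The rule also does not say which schools it applies to. Since the following sentence chooses between two interventions, it should be stated for each intervention arm.

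**What to change.** In Discussion and Conclusion, delete 'healthy' from the menu criterion, so that it matches Intervention Overview, and name the schools and the level of judgement. For example:

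> Progression requires that, in the intervention schools and judged separately for intervention 1 and intervention 2, GREEN items make up more than 50% of all items on the canteen menu, and that 80% of eligible participants are recruited.

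Optionally, report the GREEN share in the convenience shop beside the criterion, using the weekly audits already planned. It should not enter the threshold, which the authors set for the canteen. Nor should a baseline shop inventory be required: the audits run during the intervention weeks, and the menu capture in Data Collection covers canteens only.

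**Cost.** Wording only, with no new data. The threshold is harder to pass than under either literal reading, and one intervention may pass while the other does not, which is what the choice between them needs to show.

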## Ethics Statement

Ethical approval was given by the Medical Ethics Committee at University of Malaya Medical Centre, reference number 2018214-6029. Written informed consent to participate in this study was provided by the participants' legal guardian/next of kin.
